##### Depressive Symptoms

The Beck Depression Inventory-II (BDI-II) will be used. The BDI-II is a 21-item, self-report inventory designed to measure the frequency and severity of depressive symptoms. Items include somatic-affective symptoms as well as cognitive symptoms. Possible scores range from 0 (no depressive symptoms) to 63 (severe depression).

##### Anxiety Symptoms

The State-Trait Anxiety Inventory (STAI) will be used. The STAI is a self-report that assesses two types of anxiety: state anxiety, or anxiety about an event, and trait anxiety, or anxiety level as a personal characteristic. Only the 20 items referred to state anxiety will be administered. Possible scores range from 0 (no anxiety) to 60 (severe anxiety).

##### Worrying

The Penn State Worry Questionnaire (PSWQ) will be used. The PSWQ is a 16-item questionnaire that aims to measure the trait of worry. The items on the scale assess the occurrence, intrusiveness, pervasiveness, and other characterizing features of an individual’s experience with worry. The scale has been shown to identify worry, over and above anxiety and depression. Items are rated on a five-point scale: 1-Not at all typical of me to 5-Very typical of me. Possible scores range from 16 (low worry) to 80 (high worry).

#### Safety Outcome Measures^1^

##### Fatigue

Participants will respond to a first question targeting the fatigue level felt at the time of finishing the session, adapted from the Brief Fatigue Inventory (Mendoza et al., 1999): *Please rate your fatigue (weariness, tiredness) by selecting the number that best describes your fatigue right now* [Options: Scale from 0 (no fatigue) to 10 (as bad as you can imagine)].

##### Adverse Events

The safety questionnaire will include a definition of side effects as any effect that was not the intended clinical effect of the CCT, regardless of it being harmful or adverse. Participants will respond to a binary question (yes/no) to indicate whether they feel any side effect right after the session. Similarly, all participants will be also asked a binary (yes/no) question about possible adverse events they may feel. Adverse events will be defined as any undesirable experience associated with the use of the CCT platform: *Please indicate if you feel any side effect of the Computerized Cognitive Training session you have just finished, regardless of it being harmful or adverse* (Options: Yes, No); *Please indicate if you feel any undesirable experience associated with the Computerized Cognitive Training* (Options: Yes, No).

In case any participant at any moment would respond “yes” to any of the two safety questions, a member of the research team would immediately interview them in order to classify the side effect or adverse event according to its seriousness following the criteria and elements adapted from the Patient-Reported Adverse Drug Event Questionnaire (de Vries et al., 2013).

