The first cohort of participants (*N* = 3) will then start the phase I testing protocol. All participants will complete CogniFit Personalized Online Training, consisting of individual sessions in which three brain training games with a duration of around 5 min each need to be completed. The CCT will train six fundamental cognitive skills associated with the domains of memory, attention, perception and coordination: naming, working memory, non-verbal memory, visual perception, response time, divided attention and inhibition. The three participants from the first cohort will individually complete a 15-min training session under the supervision of a researcher from the team and a clinical psychologist. After finishing the session, they will complete a fatigue and safety evaluation questionnaire aimed at obtaining information about potential side effects and adverse events associated with the clinical process (see *Instruments and Outcome Measures* section). In case no side effects or adverse events are reported, a dose escalation will be implemented, and participants will then continue with a new training session of similar characteristics, structure and duration. The fatigue and safety questionnaire would be repeated right at the end of this new session, and the protocol would cyclically continue until the supervising researchers decide not to continue with an additional session because of having reached the dose-limiting toxicity level. If one participant from the cohort reports extreme fatigue levels (scores of 9 or 10 on the scale described below) or side effects or adverse events (see the questionnaire below) with a certain dose level (level i), a new cohort of three participants would start the protocol with the same dose level. If no other participant from the 3 + 3 cohort reports extreme fatigue, side effects or adverse events, the procedure would restart for a new cohort of three participants at the next dose level (level i + 1). However, if more than one participant from the 3 + 3 pool reports any of the outcomes, the maximum tolerated dose of the CCT would be set at level i-1. If two or more participants from the first cohort report extreme fatigue levels, or side effects, or adverse events with a certain dose level (level i), the maximum tolerated dose of the CCT would be set at level i-1.

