#### Phase II

This trial will include a different group of 20 patients from the same hospital who meet the inclusion criteria described above, who will also sign the corresponding consent forms prior to initiation of collaboration. After having set the maximum tolerated training time per session in the phase I trial, a 15-day phase-II trial will be designed to ascertain the effectiveness of the CCT in the absence of adverse events or side effects.

To this end, 20 patients from the Sleep Unit of the Hospital Universitario de la Ribera (Spain) will be recruited and they will first complete an initial session (Day 1) that will serve to collect baseline data about their sleep problems and their cognitive skills, as well as about their sociodemographic information. As in the phase I trial, they will complete the general cognitive and psychological evaluation lasting for around 60 min (see Instruments and Outcome Measures section).

The day after the initial evaluation (Day 2), participants will be asked to visit the Sleep Unit again to complete the first training session with the CCT. The duration of the training session will be determined by the results of the phase I trial. Participants will complete this training session using either a tablet, a PC or a laptop, accompanied by the research and clinical team. Right at the end of the session, and in order to assess the safety of the intervention, participants will also complete the same safety questionnaire as in the phase I trial. In case any participant at any moment would report potential adverse events in any of the safety questions, the clinical psychologist would immediately interview them in order to classify the side effect or adverse event according to its seriousness following the criteria and elements adapted from the Patient-Reported Adverse Drug Event Questionnaire (de Vries et al., 2013).

The protocol would then continue the next day (Day 3) with a full assessment identical to that of the first session. The day after (Day 4) would consist of the repetition of the training session of Day 2. This way, and alternating assessment and training sessions, participants will complete a 15-day cycle that will start and end with a full assessment (Day 1 and Day 15), and that will include eight different evaluation or test points (Day 1, Day 3, Day 5, Day 7, Day 9, Day 11, Day 13, and Day 15) and seven training sessions (Day 2, Day 4, Day 6, Day 8, Day 10, Day 12, and Day 14).

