The results of the effectiveness of the CCT will be evaluated using linear mixed models for repeated measures, analyzing differences in the primary and secondary outcomes described below. This will provide a first approach to and statistical validation of the usefulness of the CCT to alleviate the cognitive, psychological or medical symptoms of insomnia in the selected sample by determining the minimum number of training sessions needed to observe a significant change. Besides, quantitative and qualitative analysis of the results of the safety questionnaires will help us determine the safety of the intervention program.

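### No safety question in Phases I and II is scheduled or worded to catch delayed effects of training, such as worse sleep the following night

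*Protocol article*

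**What the plan says.** The protocol article fixes both the timing and the wording of its safety questions.

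- **Timing, Phase I:** "After finishing the session, they will complete a fatigue and safety evaluation questionnaire". If nothing is reported, a further session follows and "The fatigue and safety questionnaire would be repeated right at the end of this new session".
- **Timing, Phase II:** "Right at the end of the session, and in order to assess the safety of the intervention, participants will also complete the same safety questionnaire". On the day after training, "The protocol would then continue the next day (Day 3) with a full assessment identical to that of the first session".
- **Wording, fatigue item** (Safety Outcome Measures, Fatigue): a 0–10 rating of fatigue at the moment of answering.
- **Wording, side-effect item** (Adverse Events): "Please indicate if you feel any side effect of the Computerized Cognitive Training session you have just finished". The section states when it is asked: "Participants will respond to a binary question (yes/no) to indicate whether they feel any side effect right after the session".
- **Wording, adverse-event item** (Adverse Events): "Please indicate if you feel any undesirable experience associated with the Computerized Cognitive Training". This item is also in the present tense, but it is not tied to the session just completed.
- **Use:** in Phase II, "quantitative and qualitative analysis of the results of the safety questionnaires will help us determine the safety of the intervention program". The Phase III section then says that safety has already been established by the two earlier phases, and that no safety information will be collected in Phase III.

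**The concern.** The article's own account of insomnia (Explanatory Models; Neurobiological Bases of Insomnia) is one of cognitive and cortical overactivation that interferes with falling and staying asleep. Insomnia Treatment lists avoiding screens at night among healthy sleep habits. The intervention is a demanding task on a screen. Under the Adverse Events definition, a side effect is any effect other than the intended clinical one, so poorer sleep after training would count as one.

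Such an effect can appear only after a night has passed, and the scheduled questions come before that night. If it occurred, it could be missing from the data that set the maximum tolerated session time. That time fixes session length in Phases II and III. The effect could also be missing from the data that justify collecting no safety information during 40 self-managed home sessions in Phase III.

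**Working it through.** The plan gives no figure to reproduce. The check compares the calendar with the wording of the items.

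**Inputs**
- Phase II has 20 patients, training on Days 2, 4, 6, 8, 10, 12 and 14 (7 sessions), and assessments on Days 1, 3, …, 15 (8, of which 7 fall the day after training).
- The safety form is described for Day 2, and Day 4 repeats the Day 2 session. I read this as one form after each of the 7 sessions.
- Phase III has 8 weeks × 5 days = 40 sessions and at least two telephone calls a week.

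**Step 1: which items could pick up an earlier night**
- Fatigue: no, it asks about the present moment.
- Side effect: no, it is limited to the session just finished.
- Adverse event: possibly. It concerns the training in general, so a patient could mention a bad night, although nothing in the item prompts for sleep or for the time since the last session.

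**Step 2: Phase I**
Participants answer after a block, go on to the next block, and answer again. I read these as consecutive blocks. No contact after a night is described, so a delayed effect has no described route into the maximum tolerated time.

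**Step 3: Phase II**
- Post-training patient-nights: 20 × 7 = 140.
- Nights with a safety question listed for the next day: 0 of 140. The next-day visit repeats Day 1, which precedes any training and lists no safety form.
- Nights followed by a later form with the adverse-event item: those after Days 2, 4, 6, 8, 10 and 12, so 20 × 6 = 120 of 140 (120/140 = 86%). That form comes two days, and therefore two nights, after the session concerned.
- Nights with no later form: those after Day 14, so 140 − 120 = 20 of 140 (14%). Only the Day 15 assessment follows them.

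These counts assume that all 20 patients complete all seven sessions.

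**Step 4: Phase III**
No safety questionnaires are planned for the 40 sessions. At least 2 × 8 = 16 calls per participant check adherence and whether anything has happened. They are not designated as safety data.

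**The case against.** The other side has substantial points.

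1. **The adverse-event item is general.** A patient who slept badly after Day 2 may answer yes on Day 4, which triggers an interview. This stands, and it rules out saying that Phase II cannot capture such an event. It remains incidental: the item is in the present tense, does not mention sleep, comes two nights later, and is not asked after Day 14.
2. **Sleep is measured.** PSQI and ISI are primary outcomes, repeated the day after each Phase II session and analysed in repeated-measures models, where average worsening could appear. This also stands. But they are analysed as efficacy outcomes, and the plan does not say that an individual's worsening on them counts as a safety event.
3. **An immediate form suits the aim of Phase I.** Objectives and Hypotheses asks how long training can last before fatigue or other adverse conditions appear. End-of-block questions answer that for acute tolerance. They do not support a wider claim of safety.
4. **Phase III calls could reveal problems.** They could, informally, but the same section rules out collecting safety information.
5. **This is a condensed article, and the footnote to Safety Outcome Measures is not in the text at hand.** A fuller protocol may add follow-up. However, the article does not leave the matter open: it states when the questions are asked and how they are worded.

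**Conclusion.** The point holds as a gap in scheduling and wording. Phase I has no described route for delayed effects. Phase II has only an incidental one, available for 120 of 140 patient-nights and for none of the 20 after Day 14. Phase III collects no safety data that could make up for this. The change should be made, because the statement that safety is established goes further than the observation window supports.

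Three stronger readings are tempting, and the documents do not support them.

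- A reader might infer that worse sleep is never captured, or that none of the 140 nights is followed by any safety question. The general adverse-event item and the repeated sleep scales contradict this.
- A reader might infer that the Phase II safety conclusion rests on the questionnaires alone. The text says only that they will help determine safety.
- A reader might infer that worse sleep is the harm to which these patients are most exposed. The background makes it foreseeable, but no section ranks harms, and the trial's hypothesis is that sleep will improve.

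The documents give no rate for training-related sleep worsening, so the number of events that would be missed cannot be estimated. The conclusion rests on two readings: that the form follows every Phase II session, and that Phase I blocks run consecutively.

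**What to change.** **Phase II.** Add the two yes/no safety items and the 0–10 fatigue item to the next-day assessments on Days 3, 5, 7, 9, 11, 13 and 15. Reword them to cover the time *since your last training session, including last night*. State that the safety conclusion uses both the immediate and the next-day answers. This gives all 140 patient-nights a next-day question, including the 20 after Day 14.

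**Phase I.** Record the same items once, the next day, by telephone or online form, and report them alongside the maximum tolerated time. A participant may pass through several levels in consecutive blocks, so a next-day answer reflects the whole exposure and cannot be assigned to one level. It should therefore be reported descriptively and not written as a new escalation rule. If this contact is not added, limit the Phase I claim to acute tolerance.

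**Cost.** Three extra items at visits already scheduled in Phase II, and one short contact per participant in Phase I.

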#### Phase III

The final stage of the protocol will consist of a double-blind randomized controlled phase-III trial in which a large group of patients with insomnia recruited from the Sleep Unit of the Hospital Universitario de la Ribera, as well as from collaborating medical institutions will voluntarily enroll in an 8-weeks personalized and supervised cognitive training intervention. The medical team will inform those patients who meet the inclusion criteria of the possibility of voluntarily participating in the experiment. Those interested will be put in contact with the researchers, who will interview them individually. In this first contact, all the information regarding the study will be provided. Patients who agree to participate will complete the necessary legal documentation and informed consent and be included in the study.

A complete evaluation will be carried out at the beginning (pretest) and at the end of the intervention (post-test) using the materials and instruments also used in the phase-II study. The pretest will collect baseline data about sleep problems and cognitive skills, together with sociodemographic information. Standardized batteries and tests will be used to measure the general neurocognitive state and the emotional state, together with specific tests and measurements of the pattern and quality of sleep, and tests that measure health-related quality of life. All variables will be measured objectively (i.e., direct test scores) and subjectively (i.e., what the patient or her close associates express). The post-test will collect data on sleep problems and cognitive skills, but no additional sociodemographic data will be needed (see *Instruments and Outcome Measures* section for a description of the tools). Having already established the safety of the protocol in the phase-I and phase-II studies, no information will be collected in this regard in the phase-III trial.

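### The adverse event definition and both yes/no safety items require the patient to link the experience to the training, so unattributed events other than fatigue have no stated recording route in Phases I and II

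*Protocol article*

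**What the plan says.** The Adverse Events section of the protocol article prints the definitions and the items themselves.

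- Adverse event, definition: "Adverse events will be defined as any undesirable experience associated with the use of the CCT platform".
- Adverse event, item put to the patient (yes/no): "Please indicate if you feel any undesirable experience associated with the Computerized Cognitive Training".
- Side effect, definition: "any effect that was not the intended clinical effect of the CCT, regardless of it being harmful or adverse".
- Side effect, item put to the patient (yes/no): "Please indicate if you feel any side effect of the Computerized Cognitive Training session you have just finished, regardless of it being harmful or adverse".
- Timing: participants are asked "to indicate whether they feel any side effect right after the session".
- Follow-up: an interview takes place if a participant "would respond “yes” to any of the two safety questions". Its stated purpose is to "classify the side effect or adverse event according to its seriousness", using criteria adapted from a cited patient-reported adverse drug event questionnaire.

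The answers are used in three places. In the Phase I section, a reported side effect or adverse event, or a fatigue score of 9 or 10, is a dose-limiting outcome in the 3 + 3 rule. That rule fixes session length for Phases II and III. The Phase II section applies the same questionnaire to 20 patients and names the safety questionnaires as the basis for judging safety. The Phase III section then says "Having already established the safety of the protocol in the phase-I and phase-II studies" and on that ground collects no safety information.

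**The concern.** Recording an event and judging its cause are normally separate steps: first note what happened, then let someone qualified decide whether the intervention could explain it. Here the two are merged and the judgement is left to the patient inside a yes/no question. People with insomnia have a ready alternative explanation for a headache, low mood or agitation. If they use it, the truthful answer to both items is 'no', and no interview follows.

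What is at stake is the completeness of the safety record. These items feed the rule that sets session length. They are also the main source of non-fatigue safety data before a Phase III of 40 sessions at home (8 weeks of 5 days), in which no safety data are collected. The plan describes no later safety collection that would pick up what these items miss.

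**Working it through.** **1. Following an unattributed event through the plan.** Take a patient who has a headache after a session and puts it down to a bad night.

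- Side effect item: it asks for an effect of the session. Answer 'no'.
- Adverse event item: it asks for an experience associated with the training. Answer 'no'.
- Interview: triggered only by a 'yes'. Not held.
- Phase I rule: it counts what participants report. Not counted.
- Phase II safety conclusion: drawn from the safety questionnaires. Not included.
- Phase III: no safety data.

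The exception is fatigue. The Fatigue item asks for the current level on a 0 to 10 scale with no reference to cause, and a score of 9 or 10 is dose-limiting in Phase I by itself.

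**2. Illustration of size.** The plan gives no event rate, toxicity target or attribution share, so there is no stated figure to reproduce. Everything below rests on assumed rates, with independent patients. Let p be the true per-patient event rate at a level, s the share of events the patient attributes to the training, and q = p × s the recorded rate.

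Under the Phase I rule a level passes if 0 of 3 report an outcome, or 1 of 3 does and then 0 of 3 in the added cohort:

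P(pass) = (1 − q)³ + 3q(1 − q)² × (1 − q)³

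For p = 0.40, s = 1: 0.6³ + 3(0.4)(0.6²)(0.6³) = 0.216 + 0.432 × 0.216 = 0.309. For s = 0.5, q = 0.20: 0.8³ + 3(0.2)(0.8²)(0.8³) = 0.512 + 0.384 × 0.512 = 0.709.

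| True rate p | All attributed (s = 1) | Half attributed (s = 0.5) |
|---|---|---|
| 0.10 | 0.906 | 0.973 |
| 0.20 | 0.709 | 0.906 |
| 0.33 | 0.434 | 0.783 |
| 0.40 | 0.309 | 0.709 |
| 0.50 | 0.172 | 0.600 |

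For Phase II, the chance of recording at least one affected patient among 20 is 1 − (1 − q)²⁰, where p is now the rate over the whole cycle:

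| True rate p | s = 1 | s = 0.5 |
|---|---|---|
| 0.05 | 0.642 | 0.397 |
| 0.10 | 0.878 | 0.642 |
| 0.20 | 0.988 | 0.878 |

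**3. The offset from harmless effects.** The Phase I table leaves out the other triggers of the same rule. Suppose harmless side effects occur independently at an assumed rate h and are reported. Then q = 1 − (1 − p × s)(1 − h). With p = 0.33, s = 0.5 and h = 0.20, q = 1 − 0.835 × 0.80 = 0.332 and P(pass) = 0.431. That is practically the 0.434 obtained when every harmful event, and nothing else, is counted. With h = 0.20 and full attribution, P(pass) is 0.216. So lost harmful events still raise the pass rate when all else is held fixed, but measured against a rule that counts harmful events alone, the net effect can be nil or go the other way.

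**The case against.** A reader might infer that unattributed events are never recorded and that the Phase I and II safety verdict is therefore biased towards safe. The documents do not support that much, for these reasons.

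- **Fatigue is outside the problem.** It is rated without attribution, extreme scores are dose-limiting alone, and it is the harm that the first objective names. This stands and confines the point to other events.
- **Harmless side effects count too.** Any 'yes' to the side effect item is dose-limiting, which pushes Phase I towards a lower tolerated level. As shown above, this can cancel the under-count in the pass rate. This stands for the net direction. It does not recover a missed harmful event, and stopping for harmless effects is no substitute for recording harmful ones.
- **Staff are present.** Doctors and psychologists accompany Phase I patients throughout, and supervising researchers decide whether to go on. In Phase II, mood and sleep are re-measured on alternate days. These could bring events to light, but the plan does not describe either as a source of adverse event data: the Phase I rule counts what participants report, and the Phase II repeat assessments are assigned to effectiveness.
- **The interview may cover causality.** The cited questionnaire's elements and the footnote to the safety section are not shown, so one cannot say that relatedness is never judged. The article names only seriousness, and an interview held after a 'yes' cannot reach the patients who answered 'no'.
- **The wording may be looser than it looks.** 'Associated with' could be read as a matter of timing, and attribution is easiest right after a session. Both are possible, but the item leaves the reading to each patient.
- **Some unattributed events are truly background.** Phases I and II have no control group. This stands and bears on how the fix is framed.

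**Conclusion.** The point holds in a limited form. The printed definition and both yes/no items make the patient's own attribution a condition for recording, and no stated step catches a non-fatigue event that the patient does not attribute. Such events may be under-counted in Phases I and II, and this matters because Phase III relies on those phases to collect no safety data. It rests on text the article prints in full, not on detail left to another document.

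The net direction and size of the effect on the Phase I result are unknown. The pass probabilities (0.906 to 0.973 at a 10% true rate, 0.309 to 0.709 at 40%, with half of events attributed) are illustrations. They depend wholly on the assumed event rate and attribution share, and they omit the fatigue and harmless-effect triggers. The chance of detection in Phase II (0.878 to 0.642 for a 10% event) is assumed in the same way. This is worth correcting before the safety questionnaire is used, but it does not show that the safety conclusion will be wrong.

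**What to change.** - Reword the adverse event definition and item to cover *any undesirable experience, whether or not you think the training caused it*.
- Add a relatedness judgement to the interview already planned, as a separate field from seriousness.
- Name one interviewer role. The Phase II section gives the interview to the clinical psychologist, while the Adverse Events section gives it to a member of the research team. The two should be reconciled.
- Report all events and related events separately.
- Have the sponsor state in advance which of the two counts enters the Phase I rule, since that choice can change the result.

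The cost is one reworded definition and item, one extra interview field, and more 'yes' answers and interviews. Some of these will concern background insomnia symptoms, which phases without a control group cannot separate from effects of the training. If the all-event count fed the Phase I rule, such symptoms could lower the tolerated level, so the last item should not be left open.
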